## **Axis 2:**

- 1)** GVS would allow :
  - a)** Resynchronizing circadian rhythms (i.e. acrophase) and amplifying the sleep/wake rhythm as the procedure progresses and the cortisol rhythm at the end of the procedure.
  - b)** Improving spatial memory performance compared to T2
  - c)** Reducing hyperactivity of stress-related physiological systems
- 2)** Resynchronizing rhythms improves sleep quality
- 3)** This improvement in sleep quality is associated with better cognitive recovery and quality of life following the course of treatment, compared with the absence of GVS.

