## 8 STUDY PLAN

### 8.1 METHODOLOGY

The ICANSLEEP project is a bicentric longitudinal study.

Data from 25 patients with localized breast cancer treated with chemotherapy will be compared with those from a group of 25 patients not treated with chemotherapy and a group of 25 cancer-free volunteers (control groups), matched for sex, age and years of education (Barbizet scale).

The various evaluations will be carried out as follows:

- At T1: Approximately 1.5 months after surgery and before the start of chemotherapy in the CHI group and before the start of radiotherapy in the NCH group,
- At T2: after a delay of around 6 months, within 2 weeks of the end of chemotherapy for the CHI group, or at a distance from radiotherapy for the NCH group,
- At T3: after a two-week intervention with GVS versus non-effective stimulation (known as SHAM). To assess the effect of GVS, patients will be assigned to either the effective GVS group or the SHAM group (random selection). SHAM stimulation involves using the device but receiving a very low-frequency current that has no effect on the vestibular system. This approach has already been used and validated in the COMETE unit (Caen, [name]) with which we collaborate. All cancer-free volunteer participants will undergo GVS.

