#### 8.4.4 T1 and T2 reports

##### **In patients treated with adjuvant chemotherapy (CHI group)**

- The T1 assessment will take place after surgery and before the start of chemotherapy.
- The T2 assessment will take place 2 weeks after the end of the last session of chemotherapy.

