**Axis 2:** In order to assess the effect of galvanic vestibular stimulation on circadian rhythms, the evolution of circadian rhythm parameters measured by actigraphy during the 2-week intervention (in particular the amplitude and phase of the activity-rest rhythm) will be described by a linear mixed model. The model will include a time effect, an intervention effect (GVS or SHAM) and a time x intervention interaction (parameter of interest to assess whether GVS has an effect on the evolution of circadian rhythm compared with SHAM), and will be adjusted for group (patients or controls) and possibly treatment (chemotherapy or not). To meet secondary objectives, sleep parameters, cortisol levels, cognitive abilities and quality of life assessments will be described before (T2) and after intervention (T3) in each group of patients (GVS or SHAM) and controls (GVS only) and compared pre-post GVS by a McNemar test or a Student (or Wilcoxon) test for paired series. Alternatively, the effect of GVS on sleep, cognitive ability

and quality of life at T3 could be tested in linear or logistic models adjusted for parameters at T2.

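### For sleep, cortisol, cognition and quality of life in Axis 2, the committed test is an uncontrolled T2 to T3 comparison; the controlled model is optional, names no SHAM comparator and omits cortisol

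*Protocol*

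**What the plan says.** Protocol section 8.1 sets up the randomised comparison: "patients will be assigned to either the effective GVS group or the SHAM group (random selection"). All cancer-free volunteers receive GVS. Section 5.4 states the Axis 2 objective as a comparison with SHAM.

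Section 12.2 (Axis 2) treats two sets of outcomes differently.

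- **Actigraphy amplitude and phase.** A linear mixed model is planned. Its time by intervention interaction, GVS against SHAM, is named as the parameter of interest.
- **The other outcomes.** The text reads "To meet secondary objectives, sleep parameters, cortisol levels, cognitive abilities and quality of life assessments will be described before (T2) and after intervention (T3"). Three sets of participants are listed for this description: GVS patients, SHAM patients and the volunteers, who have GVS alone. The outcomes are then "compared pre-post GVS by a McNemar test or a Student (or Wilcoxon) test for paired series". The next sentence adds an option, under which the GVS effect on sleep, on cognition "and quality of life at T3 could be tested in linear or logistic models adjusted for parameters at T2". That option does not mention SHAM, and cortisol is not in its list.

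Section 7.1 includes cortisol in the Axis 2 main criterion, with the change in its rhythm measured from saliva at T2 and T3.

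The hypotheses in section 6 are mixed. Axis 2 hypothesis 1b is a change from T2 ("Improving spatial memory performance compared to T2"), whereas hypothesis 3 is framed relative to not having GVS.

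**The concern.** A paired T2 to T3 test asks whether anything changed over the two weeks. It does not ask whether GVS changed it. SHAM is in the design to make that distinction, and the committed analysis of these outcomes does not use it.

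The protocol itself gives reasons to expect change that both arms share:

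- **Recovery.** For the chemotherapy group, section 8.4.4 says "The T2 assessment will take place 2 weeks after the end of the last session of chemotherapy". T3 follows two weeks later, so these patients move further from chemotherapy whichever arm they are in. Section 8.1 words the T2 timing differently (within two weeks of the end of chemotherapy), and the two statements need reconciling. The argument holds under either.
- **Retesting.** The cognitive battery and the spatial memory task are repeated after two weeks. Table 6 gives different forms at each time for the HVLT and for fluency. None is listed for d2-R, TMT, Stroop, N-Back, the double task or the MEM-III subtest.
- **Sessions.** Sections 5.3 and 10.1 give both arms supervised sessions five mornings a week for two weeks, at around 9:30. A fixed, attended morning appointment could itself alter sleep or rhythms.

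At stake is whether a statement about GVS on these outcomes rests on the randomised contrast. Leaving open which analysis leads also allows the choice to be made after the results are seen.

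**Working it through.** The protocol gives no alpha, power, effect size or SD (section 12.1 says there is no power calculation), so there is no planned figure to reproduce. What follows is an illustration.

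**Inputs**

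- Patients: 50 (section 12.1). Allocation ratio not stated; 1:1 is assumed, giving 25 GVS and 25 SHAM.
- Test level: two-sided 5% (assumed).
- True GVS effect: zero.
- Shared T2 to T3 change: *d* SDs of the change score, from 0 to 0.8 (assumed; the protocol gives no value).

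**Step 1: paired test in the GVS patients.** With *n* = 25, the t statistic is noncentral t with 24 degrees of freedom and noncentrality *d*√*n* = 5*d*. The chance of significance is P(|T| > t at 0.975 with 24 df). For *d* = 0.3 the noncentrality is 1.5 and the chance is 0.302. For *d* = 0.5 it is 2.5 and the chance is 0.670.

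**Step 2: GVS against SHAM.** The change scores of 25 against 25 were compared by a two-sample t-test in 40,000 simulated trials. The same runs counted how often GVS was significant and SHAM was not, which is how two separate paired tests might be read.

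| Shared change (SD) | Paired test, GVS arm (exact) | GVS versus SHAM (simulated) | GVS significant, SHAM not (simulated) |
|---|---|---|---|
| 0 | 5% | 5.0% | 4.9% |
| 0.2 | 16% | not run | not run |
| 0.3 | 30% | 5.0% | 21% |
| 0.5 | 67% | 4.9% | 22% |
| 0.8 | 97% | 4.9% | 2.9% |

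The between-arm column is flat because a change common to both arms cancels in the difference. In a T2-adjusted model a constant shared change goes into the intercept, so it does not enter the arm effect there either.

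**Step 3: what the controlled comparison can detect.** At 80% power, (1.960 + 0.842) × √(2/25) = 2.802 × 0.283 = 0.79 SD of the change score. The noncentral t gives 79% power at 0.80 SD and 80% at 0.81 SD. Power at 0.5 SD is about 41%.

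**Step 4: which outcomes have a controlled analysis.**

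| Outcome | Committed test | Controlled option |
|---|---|---|
| Actigraphy amplitude, acrophase | Mixed model, GVS versus SHAM | Already committed |
| Sleep, cognition, quality of life | Paired pre-post | T2-adjusted model, optional, comparator not named |
| Cortisol | Paired pre-post | None named |

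**The case against.** Several points on the other side have force.

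- A reader might infer that every Axis 2 secondary outcome lacks a SHAM comparison. The protocol does not support that. Table 2 lists actigraphy amplitude and acrophase as secondary criteria for objectives 1a and 2, and these are modelled against SHAM.
- A reader might infer that no controlled analysis is foreseen for the rest. Section 12.2 does offer a T2-adjusted model for sleep, cognition and quality of life, and it would naturally carry a GVS/SHAM term. It is optional and does not say so.
- A reader might infer that shared change will be reported as a GVS effect. That is a risk, not a certainty: SHAM results are described alongside, and the paired test keeps its 5% level for its own null of no change. The error lies in reading that change as caused by GVS.
- The phrase about pre-post GVS may mean before and after in each listed group, SHAM included. Even so, no test between arms is named, and reading significance in one arm but not the other as an effect has the error rates in the last column of the first table.
- Patients and controls are listed as separate groups and no pooling is planned, so a calculation on 50 pooled GVS recipients would not reflect the protocol.
- Recovery after chemotherapy concerns 25 of the 50 patients, and alternate forms partly limit practice effects.
- The study calls itself descriptive and exploratory. That explains the missing power calculation and lowers the urgency. It does not turn an uncontrolled comparison into a test of GVS.

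A separate analysis plan could settle which option leads, but the protocol already names the uncontrolled test as the committed one.

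**Conclusion.** The point holds for sleep, cortisol, cognition and quality of life, and not for actigraphy. For these outcomes the committed test does not address the comparison with SHAM that the objective and the randomisation call for. Cortisol is the clearest case: it sits under the Axis 2 main criterion, yet section 12.2 names no controlled analysis for it.

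With a shared change of 0.3 to 0.5 SD, the false-positive risk for a claim about GVS would be about 30% to 67%, against about 5% for the arm comparison. Those figures rest on assumed shared changes, 1:1 allocation and a two-sided 5% level. The direction does not depend on them: any non-zero shared change raises the paired test's rejection rate above nominal.

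**What to change.** In section 12.2, state that the effect of GVS on sleep, cortisol, cognition and quality of life is estimated by regressing the T3 value on arm (GVS or SHAM), the T2 value and chemotherapy group (CHI or NCH). Restrict this to randomised patients and report the arm difference with its 95% confidence interval. Use the logistic version already mentioned for binary outcomes. Volunteers all receive GVS and cannot inform this contrast.

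Keep pre-post changes within each arm and in the volunteers as description. Reword Axis 2 hypothesis 1b in section 6 so that the comparison is with SHAM. The association questions in Axis 2 objectives 2 and 3 may keep their own analyses.

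The cost is text in sections 6 and 12.2, with no new data or visits. The real downside is lower precision than a paired test: with 25 per arm, only differences of about 0.8 SD of the change score are detectable at 80% power, so intervals will be wide and should be presented as such. The change should be made before any T2 to T3 comparison is run.

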### **12.3 NON-COMPLIANCE WITH PROTOCOL**

Any deviations from this protocol, as well as any modifications that may occur after the start of the study, will be discussed in the study report.

## **13 QUALITY ASSURANCE**

In order to guarantee the authenticity and credibility of data in accordance with GCP, the sponsor will implement a quality assurance system that includes:

- trial management according to Clinical Research Unit procedures,
- quality control of investigator site data by the monitor, whose role is to check the concordance and consistency of the data in the observation book with the source documents,
- the provision of dedicated staff in the department, if funding allows, to help the investigator with study logistics and data collection in observation notebooks.

## **14 ETHICAL AND REGULATORY CONSIDERATIONS**

The study will be conducted in accordance with the French Public Health Law, specially relating to biomedical research involving the human person of the Public Health Code, articles L1121-1 and following (Law No. 2012-300 of 05/03/2012 as amended by Ordinance No. 2016-800 of 16 June 2016), the Bioethics Law, the law related to the protection of physical persons for the treatments of personal data and related to information technology, database and liberties, the Helsinki declaration and the Good Clinical Practices.

### **14.1 REGULATORY APPROVALS**

A request for authorization will be sent by the Sponsor to the Comité de Protection des Personnes (CPP) before the start of the study. The Competent Authority (ANSM) will be informed, and the summary of the study and the CPP's favorable opinion will be forwarded.

This study falls within the scope of the "Reference Methodology" (MR-001) in application of the provisions of article 54 paragraph 5 of the modified law of January 6, 1978 relating to data processing, files and freedoms. This change was approved by a decision dated January 5, 2006.

The Centre François Baclesse complies with the regulations in force, in particular the rights of persons subject to processing within the meaning of EU Regulation No. 2016/679 on data protection ("RGPD").

Any substantial modification of the protocol, concerning study objectives, design, population, examinations or significant administrative aspects, will require the approval of the coordinating investigator, the sponsor, the favorable opinion of the CPP and the information of the competent authority before implementation.

## 14.2 PARTICIPANT INFORMATION AND WRITTEN INFORMED CONSENT FORM

Participants will be fully and fairly informed, in comprehensible terms, of the objectives and constraints of the study, the possible risks involved, the necessary monitoring and safety measures, their right to refuse to participate in the study or the possibility of withdrawing at any time.

All this information appears on an information and consent form given to the subject (patient or cancer-free woman). The subject's free, informed and written consent will be obtained by the investigator, or a physician representing him/her, prior to final inclusion in the study. One copy of the information and consent form signed by both parties will be given to the subject, the other copy will be kept by the investigator. For any substantial modification of the protocol, concerning the study's objectives, design, population, examinations or significant administrative aspects, a new consent from the persons taking part in the research will be obtained if necessary.

## 14.3 STUDY CONDUCT AND INVESTIGATOR RESPONSIBILITIES

The principal investigator of each institution concerned undertakes to conduct the clinical trial in accordance with the protocol approved by the CPP. The investigator must not make any changes to the protocol without the sponsor's authorization, and without the CPP having given a favorable opinion on the proposed modifications.

It is the responsibility of the principal investigator:

- ✓ provide the promoter with his curriculum vitae and those of the co-investigators,
- ✓ identify the team members involved in the trial, and define their responsibilities,
- ✓ to start recruiting patients after authorization from the sponsor,
- ✓ make every effort to include the required number of patients within the established recruitment period.

It is the responsibility of each investigator to:

- ✓ obtain the patient's dated and personally signed informed consent prior to any trial-specific selection procedure,
- ✓ regularly complete case report forms (CRFs) for each patient included in the trial, and give the sponsor's monitor direct access to source documents so that he or she can validate CRF data,
- ✓ accept regular visits from the instructor and, if necessary, auditors appointed by the promoter or inspectors from the supervisory authorities.

All study documentation (protocol, consents, case report forms, investigator file, etc....), as well as original documents (laboratory results, X-rays, consultation reports, reports of clinical examinations performed, etc.) must be made available to the sponsor or persons acting on behalf of the sponsor, and must be kept in a safe place and treated as confidential material.

Data archiving is the responsibility of the investigator, in accordance with current legislation. Documents to be archived include the protocol and appendices, including any amendments, original signed information and consent forms, questionnaires, CRFs and a patient identification list. All these documents will be kept for a minimum of 15 years after the end of the study.

#### 14.4 DATA OWNERSHIP AND CONFIDENTIALITY

The investigator undertakes, for himself and for all persons involved in the trial, to guarantee the confidentiality of all information relating to the project until publication of the trial results. This obligation of confidentiality will not apply to information that the investigator may communicate to participants as part of their participation in the trial, nor to information that has already been published.

The investigator undertakes not to publish, divulge or use in any way whatsoever, directly or indirectly, any scientific or technical information relating to the trial.

The trial may not be the subject of any written or oral comment without the sponsor's agreement; all information communicated or obtained during the trial is the property of the sponsor, who may freely dispose of it.

### 15 DATA PROCESSING AND STORAGE

#### 15.1 DATA COLLECTION AND PROCESSING

Data will be managed by the Cancéropôle Nord-Ouest's Data Processing Center (CTD). The CTD provides a database management software package dedicated to clinical research: *Ennov Clinical* (version 7.5.10, ENNOV / CLINSIGHT, 33155 Cenon, France).

This software package, based on an Oracle® database architecture, is designed for the global management of clinical and epidemiological studies, and meets the regulatory requirements linked to this type of study. The CTD's *Ennov Clinical* instance is validated in its IT environment. A data validation plan will be drawn up jointly by the Clinical Research Unit and the Data Processing Center, describing in detail the checks to be carried out for each variable.

A study-specific database will be created, tested and validated before data entry begins. All information required by the protocol must be recorded in the paper or electronic case report forms under the responsibility of the principal investigator, with an explanation given for any missing data. Data must be entered in these notebooks as they are obtained, and the sponsor will be responsible for monitoring.

The data will then be checked by the CTD in accordance with the data validation plan.

The database will be frozen after final quality control, then exported in the appropriate format for statistical analysis, using an automated, validated procedure.

Descriptive statistical analyses are planned and will be carried out before the end of the study. These will in no way interfere with the protocol.

#### 15.2 ARCHIVING

The sponsor must ensure that essential documents relating to the conduct of the study are archived in conditions that guarantee their security, for the minimum period stipulated by GCP, i.e. 15 years after the end of the research.

These documents are the protocol and appendices, including any amendments, original signed information forms and consents, questionnaires, CRFs, follow-up documents, statistical analyses and the final study report.

### **15.3 DATA OWNERSHIP AND PUBLICATION RULES**

The results of this study, the property of the promoter (Centre François Baclesse), will be published in the form of scientific articles. Publications concerning or resulting from this research will be communicated to all investigators and submitted for review by the study coordinators.

Authors will include the investigators who included the most patients, the biostatistician who carried out the data analysis (if applicable), the project leader, as well as participants who made a substantial contribution to the development of the study, to the analysis and interpretation of the results and/or to the drafting of the manuscript. No publication will be made without the agreement of the coordinator and the sponsor. The organization having contributed to the financing of the study will be mentioned in the publication.

Acknowledgements to the members of the supervisory committee will be included in the final publication.

The publication rank will be defined according to the investment made in preparing and carrying out the study.

Specific publications may be produced for ancillary studies.

These works will be the property of all the authors and will be made available to them for cross-disciplinary communications and publications.

Publications relating to the results of any ancillary studies will be subject to the prior agreement of the coordinating investigator and the methodologist; they will follow publication of the main study, which must be referenced.

## **16 FINANCING AND INSURANCE**

### **16.1 STUDY BUDGET**

Any additional costs referred to in the Public Health Code are covered by an agreement negotiated between the CFB and the establishment's representative, taking into account the financial resources available to the CFB for its public promotion activities.

However, the CFB is responsible for organizing the study and supplying the following materials (protocol, observation notebook, investigator file) needed to conduct the study.

If materials or treatments are supplied by other partners, the conditions must be specified in the study agreement.

### **16.2 INSURANCE**

The Sponsor has taken out insurance covering its own civil liability and that of any physician involved in the study for the entire duration of the study. It will also provide full compensation for any consequences of the research for the person taking part and his or her beneficiaries, unless it can prove that the damage is not attributable to its own fault or to that of any other party involved, without being able to invoke the act of a third party or the voluntary withdrawal of the person who had initially agreed to take part in the research (cf. article L 1121-10).

